## Abstract

**Introduction::**

People with visual impairment (VI) have loss of vision that causes impact on their daily living activities. Synonymous of VI are blindness, low vision, subnormal vision, visual incapacity, although there are peculiarities among them. The autonomic nervous system (ANS) provides the body with dynamic adaptation, moment by moment, according to changes in the internal and/or external body environment. As VI is an adverse condition, it is expected to be associated with changes in systemic autonomic activity, such as heart rate (HR) variability.

**Objective::**

To analyze the blindness stress by monitoring the activity of the ANS in the heart in subjects submitted acutely to low vision and also in subjects with chronic visual deficiency.

**Method::**

This is a randomized trial experimental study. In this clinical trial, initially, patients will undergo an ophthalmologic medical evaluation, along with monitoring of HR and systolic blood pressure /diastolic blood pressure. Volunteers with normal vision (Group i); and people with VI (Group ii) will be evaluated, all of them inhabitants of Rio Branco City, capital of Acre State, Brazilian Amazon. The intervention will consist of simulating blindness by sealing both eyes of each participant with good eyesight, using a sleep mask and allowing maximum occlusion for 45 minutes, split into 3 periods of 15 minutes each. Still blindfolded, participants will be requested to perform different tasks as walking, serve themselves water and/or cookies, and engaging in playful-pedagogical activity. Identical procedure will be done with the group with VI. The HR will be recorded by the Polar RS800 HR monitor. All findings with a value of *P* < .05 will be considered statistically significant. As a risk measure the odds ratio will be calculated, adjusted, and not adjusted with their respective 95% confidence intervals. The odds ratio = 1 of lowest risk for the outcome of interest will be considered as the base category for each independent variable.

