### Type, location, and population of the study

2.1

This study protocol follows the items of the Standard Protocol for Randomized Trials. It is an experimental study, specifically a randomized clinical trial on the autonomic HR modulation response, in which 50 volunteers with normal vision (Group i) and 50 individuals with visual deficiency (Group ii) have attended the Pedagogical Service of Support Center for People with VI (Fig. 1).

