**Figure 6 F6:**
[figure not shown]
Educational toys.

At each stage of 5-minute intervention activities, the patient will be monitored for their systolic and diastolic HR and level of blood glucose.

In the 3rd phase called recovery with a duration of 15 minutes, the participants will sit relaxed and resting, continuing to monitor the collection of autonomic cardiac activity through the HRV.

Participants of Group ii, after verifying their anthropometric measures, will be submitted to the same protocol of Group i.

Measurements include systolic blood pressure, DBP, mean arterial pressure, HR, and blood glucose level.

The HR monitoring for further analysis of HRV will be obtained by an HR receptor RS800CX, Polar Electro, Finland. This device was validated to locate the heart beat for HRV analysis (Fig. 7). At the appropriate moment for collection during the estimated 45 minutes of evaluation, the strap will be placed on the chest of volunteers and the HR receptor (Fig. 8), which is an equipment previously validated for HR reception, beat and use these data for HRV analysis. The receiver temporarily stores the data that will then be processed on computers.

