**Figure 8 F8:**
[figure not shown]
Placement of the belt on the patient.

The recorded pulses will be directed to a computer through an infrared signal emitting interface for analysis of the HRV by Polar Precision Performance software. For data analysis, after storage in the software, they will be filtered at a moderate intensity for the elimination of ectopic beats and/or noises. The HRV analysis will be performed in time and frequency domain (linear analysis) and also by nonlinear analysis (Fig. 9).

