### Data analysis

2.8

Data will be analyzed using the Statistical Package for Social Science, version 22.0. Descriptive analysis will be performed for all variables. Data will be expressed as mean ± standard deviation or median (interquartile range), where appropriate. Sample distribution will be tested with the Shapiro–Wilk test. For comparison of initial and final values between groups, the unpaired Student *t* test for parametric distributions and the Mann–Whitney test for nonparametric distributions will be applied. Statistical significance will be considered at the level of *P* < .05 (or 5%).

As a risk measure, odds ratio will be calculated, adjusted, and not adjusted with their respective 95% confidence intervals. The odds ratio = 1 of lowest risk for the outcome of interest will be considered as the base category for each independent variable.

Statistically significant variables in the univariate analysis will compose the model for the multivariate analysis. In this multivariate analysis, multiple logistic regression will be used (Fig. 10).

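### The protocol counts every P < .05 as significant across three HRV domains and five other measures, with no primary index or contrast, so the chance of a false positive is well above 5%

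*Protocol article*

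**What the plan says.** The rule stands in the abstract of the protocol article, under Method: "All findings with a value of *P* < .05 will be considered statistically significant". Section 2.8 (Data analysis) repeats the 5% level without qualification and does not say whether tests are one- or two-sided.

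The measures to which the rule applies are in section 2.7 (Data collection instruments):

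- HRV: "The HRV analysis will be performed in time and frequency domain (linear analysis) and also by nonlinear analysis". The number of indices per domain is not given.
- Others: "Measurements include systolic blood pressure, DBP, mean arterial pressure, HR, and blood glucose level".

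The group comparison is in section 2.8: "For comparison of initial and final values between groups, the unpaired Student *t* test for parametric distributions", with the Mann–Whitney test as the alternative. That section also selects variables for a logistic model by significance: "Statistically significant variables in the univariate analysis will compose the model for the multivariate analysis".

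The article names no primary HRV index, phase or contrast. It describes no test hierarchy or multiplicity adjustment, and it does not label the results exploratory.

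**The concern.** A 5% level limits the false-positive risk of one test. A rule that accepts every result below .05 applies that level separately to each index, and the risk of at least one false positive grows with the number of tests. With no index or contrast placed first, an autonomic effect of blindness could be claimed on whichever HRV index happens to cross .05. A reader of the results could not tell that finding from chance.

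**Working it through.** The plan states no family-wise error rate and gives no sample-size calculation, so there is no figure of its own to reproduce. Group size (50 and 50) does not enter the error rate.

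**Inputs**

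- Level per test: 0.05 (abstract and section 2.8), taken as two-sided.
- HRV domains: 3 (section 2.7). One index per domain is assumed, the smallest possible count.
- Other measures: 5, namely systolic, diastolic and mean arterial pressure, heart rate and glucose (section 2.7).
- Times compared: 2, initial and final (section 2.8). The article neither defines them nor lists the variables compared.

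**Independent tests, all null hypotheses true**

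The chance of at least one false positive in k tests is 1 − 0.95^k.

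| Tests counted | k | Chance of at least one false positive |
|---|---|---|
| One index per HRV domain, final time | 3 | 1 − 0.95^3 = 14% |
| All eight measures, final time | 3 + 5 = 8 | 1 − 0.95^8 = 34% |
| All eight measures, both times | 8 × 2 = 16 | 1 − 0.95^16 = 56% |

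For 10 and 20 independent tests the figures are 1 − 0.95^10 = 40% and 1 − 0.95^20 = 64%.

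**Correlated tests (simulation, normal test statistics, all null hypotheses true)**

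- Pairwise correlation 0.5 throughout: 29% for 10 tests, 37% for 16, 42% for 20.
- 16 tests, with correlation 0.3 to 0.5 between measures and 0.5 to 0.7 between times: 38% to 48%.
- The same correlations with an assumed three indices per HRV domain, (3 × 3 + 5) × 2 = 28 tests: 51% to 66%.

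The document gives no correlations, so these values are assumptions. The counts leave out the univariate screening for the logistic model and the measurements at each five-minute task, both of which would add tests.

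**The case against.** The strongest reply is that this is an article, and that the named index, the hierarchy and any adjustment are details for a full protocol or analysis plan that is not shown. That would answer a complaint about missing detail. It does not answer this point, because the article states a blanket rule in its abstract and repeats the level in its analysis section. A later plan that ranked or adjusted the tests would depart from that text.

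Two stronger readings are tempting, and the document supports neither.

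- *A false positive is more likely than not.* With one index per domain, that needs something like 16 independent tests, and the count is not established. Section 2.7 lists blood pressure and heart rate, but no glucose, at rest. For recovery it describes only continued HRV collection, so even the eight tests at the final time are an assumption. Mean pressure is derived from systolic and diastolic pressure. If initial means the rest phase, Group i is not yet blindfolded, and a chance difference there is no false claim of an acute effect. The introduction also expects visual impairment to alter autonomic activity, so not every null hypothesis need be true. HRV indices come from one R-R series and are unlikely to be independent. With correlation, the 16-test figure falls below one half.
- *Any of the eight measures could carry the conclusion.* The objective, section 2.1 and section 2.4 all put cardiac autonomic activity, through HRV, first. A glucose or diastolic pressure result alone would not answer that objective. The open choice is among HRV indices, phases and contrasts.

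These points reduce the size of the problem. They do not remove it: three HRV tests at one time already give 14% if independent.

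**Conclusion.** The point holds in a limited form. Followed as written, the rule gives a false-positive risk well above 5%. If tests are independent and all null hypotheses are true, the risk is 14% for the narrowest HRV-only count and 34% for eight measures at one time. The 56% for 16 tests is an upper scenario for one index per domain. Moderate correlation brings 10 to 20 tests to about 29% to 42%; several indices per domain would raise all of these figures. The number of indices, the set of comparisons and the correlations are assumptions. What rests on the text alone is the unadjusted rule and the absence of a ranking among HRV indices, phases and contrasts. This affects how every result is read and should be changed before data are seen.

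**What to change.** Replace the blanket rule in the abstract and section 2.8. Before data are seen, the investigators should:

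1. Name one primary HRV index and one primary between-group comparison, tested at two-sided 5%. Which index is for them to choose.
2. Apply Holm to one index from each of the other two HRV domains: the smaller P value is compared with 0.05/2 = 0.025 and, if that test succeeds, the larger with 0.05. This holds 5% across those two tests. To hold 5% across all three, test them only if the primary comparison is significant.
3. Report blood pressure, heart rate, glucose, initial-value comparisons and all other indices as estimates with 95% confidence intervals, labelled exploratory.

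Adjusting across everything would be a poorer choice. Bonferroni over 16 tests needs P < 0.05/16 = 0.0031. At an assumed standardised difference of 0.5 with 50 per group, power would fall from 71% at the 5% level to 32%.

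The cost is that fewer results can be called significant. It may not be wording alone: if the primary comparison is a change from rest, it differs from the comparison of initial and final values in section 2.8, and that section must be amended. No new data are needed if the chosen index comes from the recordings already planned.

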**Ethics and dissemination::**

This study will be carried out in accordance with the guidelines that regulate human research in Resolution No. 466/12 of the National Health Council. We obtained the approval of the Research Ethics Committee of the ABC Medical School/Faculdade de Medicina do ABC, with CAAE: 73945017.0.0000.0082, and Opinion No. 2,275,101. All individuals who agreed to participate in the study will sign the free and informed consent form (FICF). The FICF is also available in audio and Braille versions. The results will be disseminated through peer-reviewed journal articles and conferences. This study is registered in the Brazilian Registry of Clinical Trials under the number RBR-9sm9dp.

## Introduction

1

People with visual impairment (VI) have loss of vision that causes impact on their daily living activities. Synonymous of VI are: blindness, low vision, subnormal vision, and visual incapacity, although there are peculiarities among them.^[1]^

The prevalence and cause of blindness vary with region and time. Overall, in 1990 there were about 31.8 million blind people and 172 million people with VI. In 2010, the numbers increased to 32.4 million blind people and 191 million people with disabilities.^[1]^

The autonomic nervous system (ANS), through the sympathetic and parasympathetic divisions, provide dynamic adaptations in the body, moment to moment, according to internal changes and/or depending on alterations on the external environment.^[2]^ Since VI is an adverse condition, association with changes in systemic autonomic activity, such as heart rate variability (HRV), blood pressure (BP), changes in body temperature, and electrical conductivity of the skin, among others, is expected.^[3]^

Since cardiac function is regulated by the interaction of the sympathetic and parasympathetic branches of the ANS, HRV can be an important tool to investigate the oscillations in the intervals between consecutive heart beats (R-R intervals), which are related to the influences of the ANS on the sinus node, the natural heart pacemaker. It is a noninvasive technique, whose analysis can be performed using a linear method at time and frequency domains, or by nonlinear methods in the chaos domain^[4]^

Time domain methods use mathematically simple techniques to measure the variability present in the R-R intervals by calculating their mean and the variations of the standard deviation of heart rate (HR) over time.^[5,6]^ While frequency domain methods use spectral analysis that allows the decomposition of HR variation at a given time into its fundamental oscillatory components, that is, the time series is decomposed into different frequency components.^[7]^

In nonlinear analysis, the chaos theory approach considers systems, dynamic, deterministic, governed by nonlinear equations, and sensitive to initial conditions.^[8]^ This form of analysis may more adequately reflect changes in the autonomic modulation of biological systems, as evidence indicates that the mechanisms involved in cardiovascular regulation probably interact nonlinearly with each other.^[9]^

It is important to consider whether VI affects the cognitive and attitudes of the patients, as well as the clinical variations of the cardiac autonomic modulation, either if the low vision is acutely presented to the subject or chronically present, after a longer period of disability. In some diseases, not involving the visual apparatus, this interference in autonomic modulation may be reflected by a reduction in HRV, which has sometimes been suggestive of an indication of worse prognosis in cardiovascular diseases^[8,10]^ and related to the appearance of arrhythmias and sudden death.^[11,12]^

On the contrary, limited literature has been published about this subject, namely visual deficiency vs HRV, which strengthens and justifies the accomplishment of this research. Thereby, this study focused to analyze the blindness stress by monitoring the activity of the ANS in the heart in subjects submitted acutely to low vision and also in subjects with chronic visual deficiency.

## Materials and methods

2

### Type, location, and population of the study

2.1

This study protocol follows the items of the Standard Protocol for Randomized Trials. It is an experimental study, specifically a randomized clinical trial on the autonomic HR modulation response, in which 50 volunteers with normal vision (Group i) and 50 individuals with visual deficiency (Group ii) have attended the Pedagogical Service of Support Center for People with VI (Fig. 1).

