### Subject eligibility criteria

2.2

People of both sexes, over 18 years old, with good visual acuity, healthy, and who do not need correctional lenses, such as glasses, will be eligible to form Group i. The Group ii will be constituted by people, also over 18 years of age, both genders, with VI or blindness, with good general health, and without other physical and mental disabilities. In this context, those who present visual acuity better than 20/30 in at least 1 eye will be admitted as participant of Group i, without VI. A 2nd group with VI (Group ii), will include individuals with visual acuity less than 20/70 and greater than 20/400 in the best eye; as blind people with visual acuity worse than 20/400, finger counts at 1 m and with lack of light perception in the best eye, according to criteria of the World Health Organization.^[13]^

Individuals who do not comply the clinical criteria described or refused to participate or continue in the survey will be excluded.

Volunteers will be instructed for not drinking alcohol and/or caffeine within 24 hours prior to the intervention.

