### Data collection instruments

2.7

*First phase*: A sheet will be used to collect personal and sociodemographic data, complemented with clinical data according to the execution of medical examinations and interventions in the study participants.

Initially, it is intended to form the Group ii by searching people with VI from the Pedagogical of Support Center CAP-AC database, a public institution that exclusively provides socioeducational support services to low vision patients and the Centro de Saude Ocular (CSO), which is a private clinic of ophthalmologic care in Rio Branco City. Individuals for Group i those without VI who have good visual acuity will be invited from the CSO, seeking to match them as closely as possible with Group ii, regarding gender, age, occupation, etc.

After initial selection, volunteers will be submitted to routine clinical-ophthalmological examination, where aspects of general health will be investigated, as well as medication that may interfere with ANS, among others. Other aspects of eye health, such as visual acuity, corrective lenses, and history of ophthalmic surgery also will be evaluated.

Clinical and ophthalmological examinations that will indicate the study independent variables will be performed at the CSO, which has qualified human resources and medical equipment for anamnesis, visual acuity measurement, ocular pressure measurement, among others, with no costs for participants.

*Second phase*: In this phase, data of HRV will be collected. The protocol will be the same for both groups (Group i and Group ii). It will be divided in 3 moments of 15 minutes each: rest-intervention-recovery. After taking anthropometric measures, the participant of Group i will be given a brief rest in seated position, in a quiet environment, then the systolic, diastolic, and mean BP and HR will be measured to define a baseline condition (rest phase). Then, in the 2nd step or intervention phase, both eyes of the participant will be blindfolded with a sleeping mask that provides maximum occlusion (Fig. 5), remaining with vigilance and companionship.

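### The study is labelled a randomized trial, but visual acuity decides the group and nothing in the text is assigned by chance, so group differences are associations and the main comparison should be adjusted

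*Protocol article*

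**What the plan says.** The design label appears twice. The Method paragraph of the abstract has "This is a randomized trial experimental study", and section 2.1 has "It is an experimental study, specifically a randomized clinical trial on the autonomic HR modulation response". Section 2.1 adds "This study protocol follows the items of the Standard Protocol for Randomized Trials".

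The groups are "50 volunteers with normal vision (Group i) and 50 individuals with visual deficiency (Group ii"). Section 2.2 gives the entry rules. For the sighted group, "those who present visual acuity better than 20/30 in at least 1 eye will be admitted as participant of Group i, without VI". For the other, "A 2nd group with VI (Group ii), will include individuals with visual acuity less than 20/70 and greater than 20/400 in the best eye", together with blind people below that range.

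Section 2.7 forms Group ii by searching the support centre's database and a private eye clinic. Group i is invited from that same clinic, "seeking to match them as closely as possible with Group ii, regarding gender, age, occupation, etc". Sections 2.5 and 2.7 give both groups one procedure: rest, intervention, recovery. Within the intervention phase the tasks run in a set order: serving, walking, fitting objects.

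Section 2.8 compares initial and final values between groups by an unpaired t test or a Mann–Whitney test. Separately, it plans unadjusted and adjusted odds ratios from logistic regression, with covariates taken from those significant in univariate analysis.

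**The concern.** Random allocation is what allows a difference between groups to be read as an effect of the thing allocated. Here the label promises that property and the described procedure does not have it. Visual acuity is a trait that people bring with them, so it cannot be allocated.

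The interpretation of the main result is at stake. People with and without visual impairment may differ in other ways that bear on heart rate variability:

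- **Recruitment source.** Group ii draws on a support-service database as well as the clinic. Group i comes from the clinic alone.
- **Medication acting on the autonomic nervous system.** Section 2.7 asks about it. It is not a stated exclusion in section 2.2, a named matching factor, or a stated adjustment in the two-group tests.
- **Imperfect matching.** The matching is described as an aim, with an open-ended list of factors.

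A reader told that the trial is randomized has reason to discount all three.

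**Working it through.** The article gives no figure to reproduce on this point, so the check is textual. Each element that could have been randomised is set against what the article says about it.

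| Element | Where described | What decides it | By chance? |
|---|---|---|---|
| Person to group | 2.2 | Measured visual acuity | No |
| Person to condition | Abstract, 2.7 | Same procedure for all, so there is no alternative to allocate | No |
| Order of phases | 2.5, 2.7 | Fixed: rest, intervention, recovery | No |
| Order of tasks | 2.5, 2.7 | Fixed: serving, walking, fitting objects | No |

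Randomised elements: 0 of 4. Participants allocated by chance: 0 of 50 + 50 = 100.

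Recruitment does not change this. A database search for one group and matched invitation for the other is how a non-randomised comparison is assembled. The contrast between phases within a person is a before-during-after comparison and is not randomised either.

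Next, does the planned analysis deal with the resulting confounding?

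1. The comparison of initial and final values in section 2.8 uses unpaired two-sample tests. No covariate is named for them, and the matching sought in section 2.7 plays no part.
2. Adjustment appears only for the odds ratios. Covariates enter that model when they are significant univariately. A matching factor or known confounder that misses significance would be left out, although it may still distort the group contrast.

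So the design is non-randomised, and the stated continuous group comparison carries no adjustment.

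**The case against.** **An article condenses a fuller protocol, and several flowcharts are not shown.** This would answer a complaint that the allocation method is missing. It does not answer a contradiction: no further document or figure can make visual acuity randomly allocated. A flowchart might show random sampling from the database, but sampling is not allocation.

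**Confounding is partly handled.** This is true. Matching covers gender, age and occupation, good general health is required, medication is enquired about, the clinic supplies some of both groups, and adjusted odds ratios are planned. These steps may reduce confounding. They do not make the label true, and the adjustment does not reach the t or Mann–Whitney comparison.

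**The article makes no explicit causal claim.** This is also true. The objective and section 2.4 speak of analysing and comparing. The causal reading comes from the label, which is why the label needs correcting.

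Four stronger readings are tempting, and the document does not support them:

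- *That the two-group tests are invalid without randomisation.* They are ordinary tests for two independent samples. Randomisation bears on how the difference is interpreted, not on whether such a test may be used.
- *That the confounding can be given a size.* The article provides no standard deviation, effect size or expected imbalance, so any inflated error rate would rest on an invented input.
- *That the task order ought to be randomised.* No aim of comparing the tasks with one another is stated, and an order common to both groups does not by itself bias the group contrast. This is a separate design preference.
- *That the registry entry is wrong.* Only its number is given.

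**Conclusion.** The point holds. The abstract and section 2.1 state a design property that the rest of the article rules out: none of the 100 planned participants, and none of the four elements checked, is assigned by chance. Group i versus Group ii differences are associations, and the main continuous comparison is planned without adjustment or use of the matching. The direction and amount of any confounding cannot be given from the document.

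The conclusion rests on the text as published. It assumes only that visual acuity defines the groups, as section 2.2 says. It does not depend on the sample size, the power or the significance level. Correcting the label changes no group, measurement or sample size. It does change what the study can be said to show, so it should be settled before results are reported.

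**What to change.** 1. In the abstract and section 2.1, replace the randomized (clinical) trial label with: non-randomised two-group comparative experimental study with repeated measures.
2. In section 2.1, correct the statement that the protocol follows a standard for randomized trials, so that it no longer implies random allocation.
3. State, in section 2.1 or 2.8, that contrasts between Group i and Group ii are associations.
4. In section 2.8, make the between-group HRV estimate one adjusted for the matching factors already sought (age, sex, occupation), for example by linear regression with group and these factors as terms. Name the factors in advance and do not select them by univariate significance.

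Items 1 to 3 cost only wording. Item 4 needs a little more analysis. Section 2.7 already plans to collect sociodemographic data and to match on these three factors, so no new measurement should be needed.
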